## Methods

### Study Design

The Smoking or Nicotine Phenotype and Severity of Clinical Presentation at the Emergency Department (SMOPHED) study is an observational study with no intervention or randomization, analyzing the association between the patient’s health condition during an ED visit as well as the outcome (hospitalization and death) and different patterns of nicotine products use. Specifically, the study will explore relevant associations according to the smoking and ENDS product use status (current, former, and never use). The pilot phase of the study will take place at a single clinical center, aiming to evaluate its feasibility and analyze the results. Upon successful completion, there are plans to expand the study into a multicenter format involving a national network comprising 10-12 EDs.

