### Data Collection

On arrival at the ED, each patient undergoes a triage phase. A nurse is usually responsible for evaluating the severity of the health condition and the priority for clinical assessment (unless the patient enters the ED by ambulance under a red code). The nurse usually performs this task by collecting vital signs and recording the patient’s medical history. This information is then used to assign a color code representing the priority for further assessment. The patient then waits for the medical evaluation in a dedicated room where nurses can monitor the clinical condition of all attending patients. Participants who meet the inclusion criteria will be recruited during this phase and will be administered an electronic questionnaire (see Multimedia Appendix 1) about their smoking and nicotine product use habits and their medical history. This questionnaire serves to typify the patient’s use phenotype and quantify exposure to each product.

In addition to the questionnaire, medical data recorded at the triage phase, such as the NEWS, heart rate, blood pressure, blood oxygen saturation, respiratory rate, temperature, and fraction of inspired oxygen, will be collected.

After the assessment and management of each patient in the ED, the final diagnosis, final disposition, and color code at discharge or admission to a ward will be recorded (see Table 1). To avoid compromising the health of patients with severe disease requiring urgent medical attention, potential participants who arrive at the ED under a red code (ie, with a severe acute illness) will be asked to participate only after they are stabilized (ie, the questionnaire, NEWS, and vital signs will be recorded later).

Based on the responses to the questionnaire, participants will be divided in the following 5 smoking subgroups to facilitate analysis: (1) current tobacco smoker, (2) former tobacco smoker, (3) former tobacco smoker now using e-cigarettes and HTPs (exclusive use), (4) current tobacco smoker also using e-cigarettes and HTPs (dual use), and (5) never smokers or e-cigarette/HTP users.

After 1 month, data in the electronic case report form (eCRF) will be extracted for the statistical analysis.

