### Endpoint and Outcomes

The primary endpoint of the study is the association between the NEWS and product use phenotypes. Our hypothesis is that use of ENDS may be associated with a lower NEWS compared to cigarette smoking. If our hypothesis will be confirmed, the study will be replicated as a multicenter study to validate our findings.

Secondary outcomes will be hospital admissions (vs discharge) and length of stay in the ED and in the hospital (if admitted). Moreover, we will compare the prevalence of acute diseases known to be related to smoking between groups, specifically stroke, acute myocardial infarction, peripheral artery diseases, chronic obstructive pulmonary disease, asthma, and respiratory infections.

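### Product groups rest on status reported after the presenting illness began, which leaves an unacknowledged route for reverse causation in the NEWS comparison

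*Protocol article*

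**What the plan says.** Protocol article, Data Collection: patients are approached while they wait after triage. "Participants who meet the inclusion criteria will be recruited during this phase and will be administered an electronic questionnaire". The exposure variable comes from it: "Based on the responses to the questionnaire, participants will be divided in the following 5 smoking subgroups to facilitate analysis". The third group is "former tobacco smoker now using e-cigarettes and HTPs (exclusive use"; the others are current smoker, former smoker, dual user and never user. Statistical Analysis repeats the same five groups as the classification to be analysed. Study Design puts it in the same terms: "the study will explore relevant associations according to the smoking and ENDS product use status (current, former, and never use".

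On the questionnaire's content, Data Collection says only: "This questionnaire serves to typify the patient’s use phenotype and quantify exposure to each product". The instrument is Multimedia Appendix 1, which is not shown.

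Endpoint and Outcomes: "The primary endpoint of the study is the association between the NEWS and product use phenotypes", and "Our hypothesis is that use of ENDS may be associated with a lower NEWS compared to cigarette smoking". Replication across several centres is made conditional on confirming that hypothesis.

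Statistical Analysis names age, sex, education, past medical history and the smoking status of ENDS users as adjustment variables. The limitations in the Discussion cover season and locality, self-report without biochemical verification, recall, and late approach to critical patients.

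**The concern.** NEWS measures how ill the patient is at this visit, and the exposure label is fixed at the same visit, after that illness has begun. The diseases of interest include COPD, asthma, respiratory infection and myocardial infarction. Their symptoms can plausibly make a smoker stop, or move to an e-cigarette or heated tobacco product, before attending. Under the stated rule that patient leaves the smoker group and enters the former-smoker or exclusive-ENDS group because of the illness that then produces the NEWS.

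The exclusive-ENDS group is expected to be small, so a few such patients can move its mean. If they are sicker than stable users, the comparison tilts against ENDS. A real difference could be hidden, or an apparent harm created, in the contrast that decides whether the study is replicated.

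**Working it through.** **1. What the stated rule allows.**
- Timing of ascertainment: after triage, hence after onset of the presenting illness (Data Collection).
- Basis of the groups: current, former or now using (Data Collection, Study Design, Statistical Analysis).
- Pre-onset reference time, or minimum time since quitting or switching: none stated in any of the three sections.
- Adjustment: past medical history describes earlier disease, not a change of product prompted by the current one. Adjusting for the smoking status of ENDS users relies on the same reported status.
- Limitations: recall and self-report are named; reverse causation is not.

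**2. Expected group sizes.** The article gives no figure for this bias, so there is none to reproduce. Inputs are from Study Population (22.5% current smokers, about 5% ENDS users, about half of them dual) and Results (901 enrolled).
- Exclusive ENDS: 901 × 0.05 × 0.5 = 22.5, about 23.
- Smokers without ENDS: 901 × 0.225 − 22.5 = 202.7 − 22.5 = 180.2, about 180.
- At the planned 2000: 2000 × 0.05 × 0.5 = 50, and 2000 × 0.225 − 50 = 400.

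These are population rates applied to an ED sample, so the counts are rough. The 22.5 also includes any never-smoking ENDS users, who do not belong in the third group.

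**3. Shift in the exclusive-ENDS mean.** Let f be the share of that group who switched because of the presenting illness, and D their excess NEWS over the other members. Neither is in the document. Assume f = 5–30% and D = 1–3 points.

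Shift = f × D.
- Lowest: 0.05 × 1 = 0.05.
- Middle: 0.10 × 2 = 0.20.
- Highest: 0.30 × 3 = 0.90.

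In patients, 5–30% of 22.5 is about 1 to 7. One patient shifts the mean by D/22.5, that is 0.04 to 0.13 points.

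**4. Shift in the contrast with smokers.** Returning m = f × 22.5 patients to the smoker group raises its mean by m × D/(180.2 + m), taking the two groups as otherwise equal.
- Lowest: m = 1.1, giving 0.006; the contrast changes by 0.05 + 0.006 ≈ 0.06.
- Highest: m = 6.8, giving 0.108; the contrast changes by 0.90 + 0.108 ≈ 1.01.

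Nearly all of the effect lies in the small group.

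**5. Scale.** The article gives no SD or target difference. With an assumed SD of 2–3, two-sided 5% and 80% power, the detectable difference is SD × √(1/180.2 + 1/22.5) × 2.80 = SD × 0.626, or 1.25–1.88 points. At 2000 it is SD × √(1/400 + 1/50) × 2.80 = SD × 0.42, or 0.84–1.26. The standard error of the exclusive-ENDS mean at 901 is SD/√22.5 = 0.42–0.63.

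**The case against.** The strongest reply is that the operative definitions sit in the questionnaire, which is not shown. It may set a minimum duration for former or exclusive use, or record quit and switch dates. That stands as a caveat: the article's rule uses neither, but the data to repair it may already exist.

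Second, every input to the size is assumed, and over much of the range the shift is below one standard error of the group mean. The univariate test is Kruskal-Wallis, so a shift in means does not carry over directly. This also stands. A reader might infer that the primary contrast has been shown to be wrong; the document supports only a route for bias.

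Third, past medical history partly captures chronic lung disease. It does so for long-standing disease, not for a change made in the days before attending.

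A reader might also infer that red-code patients are badly misclassified through enforced abstinence in hospital, since they "will be asked to participate only after they are stabilized (ie, the questionnaire, NEWS, and vital signs will be recorded later". The document does not support this. Data Collection has records completed by the end of the shift, or the day after arrival for longer stays. Nothing suggests that a habitual smoker asked about habits after such a delay would be recorded as a former smoker.

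Finally, a sensitivity analysis is often left to an analysis plan that is not shown. Its absence is not the point here; the point is the grouping rule that the article does state.

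**Conclusion.** The concern holds as a design weakness that should be dealt with, not as a measured error. The stated grouping allows illness-prompted quitters and switchers to be counted as former smokers or exclusive ENDS users in the primary NEWS comparison, and neither the named covariates nor the listed limitations cover this.

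The size is unknown. Under the assumed 5–30% share and 1–3 point excess, the exclusive-ENDS mean rises by about 0.05–0.9 points. The upper end approaches the smallest difference the study could detect at 901; the lower end is negligible. The direction is probably against the study hypothesis, provided that recent switchers are sicker than stable users. The conclusion also assumes that the questionnaire does not already impose a pre-onset or minimum-duration definition.

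**What to change.** - **For the 901 enrolled, where quit or switch timing is recorded:** add a sensitivity analysis of the primary contrast that returns to their previous group, or excludes, those who changed product within a fixed window before the visit (for example 30 days). Fix the window before analysis.
- **Where timing is not recorded:** state reverse causation as a limitation and soften the conclusion accordingly. Rewording the question cannot help patients already interviewed.
- **For the multicentre phase:** word the status question to refer to use before onset of the presenting symptoms, and assign the five groups from that answer.

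The cost is one extra analysis and one reworded item. A few patients leave an already small group if they are excluded, and both onset and timing are self-reported, which adds to the recall error the article already acknowledges. A short window does not reach patients who quit long before because of the chronic disease behind the visit, so that part remains a limitation.

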**Vital signs recorded during triage**			
	Heart rate	Beats per minute	
	Blood pressure	mmHg	
	Blood oxygen saturation	%	
	Respiratory rate	Breaths per minute	
	Body temperature	°C	
	Fraction of inspired oxygen	%	
Smoking questionnaire			See Multimedia Appendix 1
Medical history and drug use history			Textual
Length of stay in the ED^b^ or in the hospital (if admitted))			Hours and minutes, or days if admitted
Final diagnosis of discharged patients			Textual
Final disposition			Admitted/discharged
Final diagnosis of admitted patients			*ICD-9*^c^ codes

^a^NEWS: National Early Warning Score.

^b^ED: emergency department.

^c^*ICD-9: International Classification of Diseases, 9th edition*.

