Since the ED is usually very crowded, four study team personnel will work on the study and will screen and recruit patients during the waiting period before the medical examination. The study team will interview potential participants in a dedicated room within the ED area to guarantee privacy. The initial survey will last approximately 5 minutes per patient. This is a reasonable time to collect product use information from each participant. After the medical visit and final disposition, compilation of the eCRF will be completed as provided by the study protocol, with each study member collecting all necessary information about the patients’ outcome (discharge or admission to a ward) by the end of their shift. Some patients may stay in the ED beyond the length of a diurnal shift; in such a case, the data will be collected the day after their arrival. Some patients might access the ED two or more times during the study. To avoid double entries, only the first visit will be included for analysis in the study. The eCRF database will reply with an error if we try to recruit a patient with the same fiscal code a second time (a fiscal code is a unique identifying code in Italy, and it is mandatory to be recorded for each patient during the triage phase in the ED).

**Table 1 table1:** Data to record in the electronic case report form.

Data type			Value/units
NEWS^a^ calculated at the patient’s triage phase (conventionally, patients with an acute condition will be recorded as being at high risk, corresponding to NEWS>7)			0-17

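### Table 1 as written provides no ED length of stay for admitted participants, although ED length of stay is a secondary outcome for everyone

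*Protocol article*

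**What the plan says.** Under Endpoint and Outcomes the article states: "Secondary outcomes will be hospital admissions (vs discharge) and length of stay in the ED and in the hospital (if admitted". The condition about admission attaches to the hospital part alone, so ED stay is an outcome for every participant.

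Table 1 in Data Collection carries the title "Data to record in the electronic case report form". It has one row for length of stay. The label names the ED and then continues "or in the hospital (if admitted", and the value column reads "Hours and minutes, or days if admitted".

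The Data Collection text says that staff gather the patient's "outcome (discharge or admission to a ward) by the end of their shift", or on the following day for patients who remain in the ED longer. ED duration is not named there. Ethical Considerations adds that two linked databases allow outcome or missing data to be entered later. Statistical Analysis plans regressions of the secondary outcomes on product use.

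**The concern.** The outcome definition joins two quantities with *and*. The data item joins them with *or*, and its unit changes with admission status. Someone completing the form literally would enter ED time for a discharged patient and days for an admitted one, leaving no place for the admitted patient's time in the ED.

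Two analyses would then be possible, and neither estimates the stated outcome. ED stay could be compared among discharged patients only, which conditions on admission, itself compared between product groups. Or the single item could be used for everyone, mixing ED hours with hospital days. The Discussion presents the burden on emergency care resources as a direct implication of the study, and the ED time of admitted patients is part of that burden. Study Design foresees expansion to 10-12 EDs, so an uncorrected item could carry over.

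**Working it through.** The documents give no length-of-stay mean, SD or admission rate, so there is no figure to reproduce. The check is a comparison of texts, followed by arithmetic on assumed inputs.

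**1. Outcome against data item**

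- Outcome (Endpoint and Outcomes): "length of stay in the ED and in the hospital (if admitted". Needed: ED stay for all, plus hospital stay for those admitted.
- Data item (Table 1): one row, ED or hospital, with the unit "Hours and minutes, or days if admitted".
- Provided by a literal reading: discharged patients, ED time; admitted patients, hospital days. Missing: ED time for admitted patients.

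**2. Could ED time be derived from other listed items?** Table 1 lists no ED arrival time, ED departure time or separate ED duration.

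**3. Is one row simply the table's style?** Where the final diagnosis differs by disposition, Table 1 gives two rows: "Final diagnosis of discharged patients" and "Final diagnosis of admitted patients". Length of stay is not split in this way.

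**4. How many participants could be affected?** Enrolled: 901 (Results section). Assumed proportion admitted: 15% to 30%.

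- 901 × 0.15 = 135
- 901 × 0.30 = 270

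**5. What would restriction to discharged patients do?** All inputs in steps 5 and 6 are assumptions: 30% of smokers and 15% of ENDS users admitted, with the ED durations below.

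Scenario A: ED stay is 4 h if discharged and 10 h if admitted, in both groups.

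- Smokers, all: 0.70 × 4 + 0.30 × 10 = 5.8 h
- ENDS users, all: 0.85 × 4 + 0.15 × 10 = 4.9 h
- Difference in all participants: 0.9 h; in discharged patients: 4.0 − 4.0 = 0 h

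Scenario B: ED stay if discharged is 5 h (smokers) and 4 h (ENDS users), and 3 h if admitted in both groups.

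- Smokers, all: 0.70 × 5 + 0.30 × 3 = 4.40 h
- ENDS users, all: 0.85 × 4 + 0.15 × 3 = 3.85 h
- Difference in all participants: 0.55 h; in discharged patients: 5 − 4 = 1.0 h

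Restriction removes the difference in A and enlarges it in B. The direction depends on inputs that the documents do not give.

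**6. What would mixing the units do?** Take scenario A with an assumed hospital stay of 7 days (168 h) entered in place of ED time.

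- Smokers: 0.70 × 4 + 0.30 × 168 = 53.2 h
- ENDS users: 0.85 × 4 + 0.15 × 168 = 28.6 h

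Almost all of the 24.6 h gap comes from the difference in admission rates.

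**The case against.** The strongest reply is that a table row in a journal article is not an eCRF field. The eCRF is not shown. Other rows bundle several items: the smoking questionnaire is one row, and medical history shares a row with drug use. Table 1 is also not exhaustive: Data Collection refers to it for the color code at discharge or admission, yet no such row appears. The length-of-stay row can be read as shorthand for two quantities, each with its own unit, which would agree with the outcome definition. The linked databases permit later completion. Nothing in Statistical Analysis proposes averaging hours with days, and final disposition is recorded, so the two kinds of value could be told apart.

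Much of this stands. A reader might infer that the ED time of admitted patients is never captured; the documents do not support that, because no section says that it is omitted and later completion is foreseen. A reader might also infer that the smoker-versus-ENDS contrast is pulled towards no difference; scenario B shows that this does not follow.

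The conflict itself remains. The article states a recording rule that differs from its own outcome definition, and the two diagnosis rows make the shorthand reading the weaker one. Permission to add data later does not put ED time for admitted patients on the list of data to record. Separating the two kinds of value by disposition still leaves admitted patients without an ED time.

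**Conclusion.** The point holds as an inconsistency between the outcome definition and Table 1. Followed literally, Table 1 does not provide ED length of stay for admitted participants, so this secondary outcome would be confined to discharged patients or would mix two quantities. Whether data were actually lost cannot be judged without the eCRF.

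The size is unknown. The 135 to 270 participants and the hour figures rest on assumed rates and durations and serve only as illustration; the direction of any bias is likewise unknown. The matter concerns one secondary outcome in a declared pilot and leaves the primary endpoint, NEWS, untouched. It should still be corrected, because an analysis plan cannot recover a time that was not recorded.

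**What to change.** Reconcile Table 1 with Endpoint and Outcomes by replacing the single row with two:

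- (a) ED length of stay, in hours and minutes, from ED arrival to leaving the ED, for every participant including those admitted;
- (b) hospital length of stay, in days, for admitted participants only.

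Analyse (a) in all participants and (b) in admitted participants.

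Then check the eCRF used for the 901 enrolled. If it did not capture (a) for admitted participants, complete it from ED record times through the linked ID database described under Ethical Considerations. If it already holds both, correcting Table 1 is sufficient.

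The cost is at most one extra field and a record look-up, with no new patients or procedures.

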### Endpoint and Outcomes

The primary endpoint of the study is the association between the NEWS and product use phenotypes. Our hypothesis is that use of ENDS may be associated with a lower NEWS compared to cigarette smoking. If our hypothesis will be confirmed, the study will be replicated as a multicenter study to validate our findings.

Secondary outcomes will be hospital admissions (vs discharge) and length of stay in the ED and in the hospital (if admitted). Moreover, we will compare the prevalence of acute diseases known to be related to smoking between groups, specifically stroke, acute myocardial infarction, peripheral artery diseases, chronic obstructive pulmonary disease, asthma, and respiratory infections.

### Statistical Analysis

Descriptive analysis will be performed by presenting numerical data as mean (SD) and categorical data as n (%). Patients will be classified according to product use as a current tobacco smoker, former tobacco smoker, former tobacco smoker now using e-cigarettes and HTPs (exclusive use), current tobacco smoker also using e-cigarettes and HTPs (dual use), and never smokers/never e-cigarette or HTP users.

Univariate comparisons will be performed using *χ*^2^ tests for categorical variables and the Kruskal-Wallis H test for the NEWS. Regression analyses will be performed to examine the association between the use of different types of products and the NEWS as well as secondary outcomes. Demographics, including age, sex (male or female), and educational level, as well as past medical history will be included as independent variables. Since the majority of ENDS users report current or past smoking, the smoking status of these users will also be recorded along with those who do not report any ENDS use. Therefore, the analysis will be adjusted for the smoking status of ENDS users. Additionally, secondary analyses will be performed for never-smoking ENDS users, if a sufficient number of such participants will be available. All analyses will be performed using SPSS v.25 (IBM) and a *P* value <.05 will be considered statistically significant.

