### Study Population

Inclusion and exclusion criteria are summarized in Textbox 1. Participants will be recruited among patients presenting at the ED of Policlinico Teaching Hospital of Catania, Italy, in 1 month during the diurnal shift. Only patients that access the ED for a nontraumatic reason will be screened, since it is unlikely that smoking or use of other nicotine products can have any causal effect on accident incidence and subsequent diagnosis. The study will take place during daytime working hours owing to organizational constraints. Typically, our ED admits approximately 70-80 patients for nontraumatic issues during a daytime shift, which runs from 8 AM to 8 PM.

We calculated the expected sample size for the study based on available national and regional statistics, providing a practical approach to estimating the study’s sample size. The current and former smoking rates in Sicily are estimated at 22.5% and 13.3%, respectively [25], while the combined prevalence of combustion-free products use (e-cigarettes and HTPs) stands at approximately 5% [26]. Considering the annual Catania ED access rate of 80,000 (monthly access rates of 6000-6500) [27], we anticipate recruiting no less than 1500 current smokers and 1000 former smokers per month. Additionally, we expect to enroll no less than 350 users of combined e-cigarettes/HTPs per month (dual usage is estimated at approximately 50% of the total). Since approximately 70 patients per day access the ED during the diurnal shift for nontraumatic reasons, we expect to enroll approximately 2000 participants in 1 month.

Inclusion and exclusion criteria for study participation.Inclusion criteriaAdult (aged≥18 years)Ability to understand and sign the informed consent formExclusion criteriaAccessed the emergency department for a traumatic accidentPregnancy

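### Chi-squared tests are fixed for six disease comparisons whose exclusive-ENDS and dual-use cells expect about one case or fewer, which modestly inflates false positives for diseases at about 1% prevalence or below

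*Protocol article*

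**What the plan says.** The Statistical Analysis section sets univariate comparisons as χ² "tests for categorical variables and the Kruskal-Wallis H test for the NEWS", and for all analyses a P "value <.05 will be considered statistically significant". It names no alternative for small expected counts.

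Under Endpoint and Outcomes, the authors add that "we will compare the prevalence of acute diseases known to be related to smoking between groups". Six conditions are then listed: "specifically stroke, acute myocardial infarction, peripheral artery diseases, chronic obstructive pulmonary disease, asthma, and respiratory infections". The groups come from Data Collection, where "participants will be divided in the following 5 smoking subgroups to facilitate analysis". One of the five is exclusive use of e-cigarettes or heated tobacco products (ENDS) by former smokers, and another is dual use by current smokers.

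Study Population gives the rates that determine the size of those two groups: "the combined prevalence of combustion-free products use (e-cigarettes and HTPs) stands at approximately 5" per cent, and "dual usage is estimated at approximately 50% of the total". The Results section reports 901 enrolled, against about 2000 planned.

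A second layer of analysis is also planned: "Regression analyses will be performed to examine the association between the use of different types of products and the NEWS as well as secondary outcomes". The type of regression is not stated. The only place where the protocol makes an analysis depend on having enough participants is the secondary analysis of never-smoking ENDS users.

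**The concern.** The chi-squared P value rests on a large-sample approximation that is usually trusted only when expected counts are about 5 or more. Several of the listed diseases may account for a small share of visits, and two of the five groups are small. When both hold, the nominal 5% error rate is no longer guaranteed.

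The smallest groups are also the ones that the study is about. For a rare disease, a significant five-group table could come from two patients who happen to be ENDS users, and could then be read as a signal for or against these products.

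**Working it through.** **The protocol's own figure.** It expects at least 350 ENDS users per month. Its rate times its monthly accesses gives 5% × 6000 = 300, 5% × 6500 = 325, and 5% × (80,000/12) = 333, so 350 is not reproduced. The figure must refer to all accesses and not to the enrolled sample, because 1500 + 1000 + 350 = 2850 exceeds the planned 2000. The group sizes below therefore apply the rates to the enrolled number.

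**Group sizes at 901.**
- ENDS users: 901 × 5% = 45, of which half are exclusive and half dual: 22.5 each, taken as 23.
- Current smokers only: 901 × 22.5% − 22.5 = 180.
- Former smokers only: 901 × 13.3% − 22.5 = 97.
- Never users: 901 − 180 − 97 − 23 − 23 = 578.

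**Expected cases and false-positive rate.** Disease prevalence is an assumption, so a range is shown. Expected cases are 23 × prevalence. The rate is the share of simulated null tables (equal prevalence in all five groups) in which the Pearson test with 4 degrees of freedom gives P<.05. Ranges cover repeated runs, with 22 or 23 exclusive users.

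| Assumed prevalence | Expected cases, exclusive users | False-positive rate, N=901 | Same, N=2000 |
|---|---|---|---|
| 0.5% | 0.12 | 9.2-9.6% | 7.0% |
| 1% | 0.23 | 6.8-6.9% | 6.1% |
| 2% | 0.46 | 6.2-6.3% | 5.5% |
| 3% | 0.69 | 5.8-6.1% | 5.3% |
| 5% | 1.15 | 5.3-5.4% | 5.2% |
| 10% | 2.3 | 5.0% | 5.0% |

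At 1% prevalence, four of the five disease-present cells expect fewer than 5 cases (1.8, 0.97, 0.23 and 0.23; the never users expect 5.78). At 5%, three do (4.85, 1.15 and 1.15).

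**How many cases drive a significant result?** This is the chance that the five-group test is significant, given the number of cases among exclusive users (N=901):

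| Assumed prevalence | Given 1 case | Given 2 cases |
|---|---|---|
| 0.5% | 35% | 100% |
| 1% | 8% | 88% |
| 2% | 4% | 23% |
| 3% | 3% | 7% |
| 5% | 3% | 3% |

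With the other groups at their expected counts, P<.05 needs 2 exclusive-user cases at 1% prevalence, 3 at 2%, 4 at 3% and 5 at 5%. Two cases at 1% are themselves uncommon: 253 × 0.01² × 0.99²¹ ≈ 2%. That is why the overall excess stays small.

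**Exact version.** Referring the same statistic to its exact (Monte Carlo) distribution gives a rate of about 4.5% to 5% across these prevalences.

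**Empty cells.** The chance of no case among 23 exclusive users is 0.99²³ = 79%, 0.98²³ = 63% and 0.95²³ = 31% at 1%, 2% and 5%. If the planned regressions are ordinary logistic models, that group then has no finite odds ratio.

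**Sensitivity to the group size.** Taking 350 out of 6000-6500 as the ENDS rate gives 24-26 exclusive users and 1.2-1.3 expected cases at 5%. Taking 350 out of 2000 gives about 79 exclusive users and 3.9 cases, still below 5. With 2000 enrolled there would be 50 exclusive users and 0.5 to 2.5 cases at 1% to 5%.

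**The case against.** The strongest reply is that switching to an exact test for sparse tables is routine analysis-plan detail. The article condenses its methods, the full plan is not shown, and the chi-squared test is only the univariate step before adjusted regression. This lowers the weight of the point but does not remove it. The article does not leave the test open: it names one for all categorical variables, and that test fits these tables badly.

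It is also fair that the inputs are uncertain. No prevalence is given for any of the six diseases, and the 22-23 exclusive users come from population rates and are not an observed count. A disease at 10% of visits would be tested at the correct size.

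A reader might infer that one or two cases can create false significance for any disease up to 5% prevalence. The figures do not support this: at 3% to 5%, one or two exclusive-user cases lead to significance in only 3% to 7% of tables, about the nominal rate. A reader might also suppose that a direct comparison of exclusive users with smokers is inflated. The protocol specifies no such pairwise test, and its simulated rate without continuity correction is 3.7% to 5.2%.

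The remark on logistic regression is conditional, because the model type is not stated. Empty cells are at root a sample-size problem, and no method adds information to them.

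**Conclusion.** The point holds as a minor one. The named test is unreliable for the disease comparisons because the two ENDS cells expect about 0.2 to 1.1 cases at an assumed 1% to 5% prevalence. The excess in false positives is modest: about 9-10% at 0.5% prevalence, 7% at 1%, 6% at 2-3%, and near nominal from 5% upwards. Only at about 1% or below can one or two exclusive users produce a significant table by themselves.

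This rests on three assumptions: the 5% and 50% rates apply to those enrolled, all 901 are analysed, and prevalence is equal across groups under the null. It does not show that a significant result would be false in general. Nor would a significant five-group test show that ENDS users are the group that differs.

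**What to change.** In Statistical Analysis, state that the six disease comparisons, and any table with an expected count below 5, will use the Fisher-Freeman-Halton exact test or a Monte Carlo exact chi-squared test. Keep the chi-squared test for the remaining tables. Add that, if the regressions for these diseases are logistic, Firth penalisation or exact intervals will be used where an ENDS group has no cases.

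The cost is a sentence or two of text and slight conservatism. The protocol names SPSS v.25 for all analyses, so check that the installation offers these methods and widen the software statement if it does not. The Results section describes the data as still to be analysed. If that remains so, the change can be made before any result is seen; if not, report it as a post hoc change.
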